## Methods

### Trial Design

The HIS-UK study is a randomized, controlled, superiority trial with 3 parallel arms (2 intervention and 1 control arm, with a 1:1:1 allocation), with an internal pilot. A repeated measures trial design is being used with baseline measurement (T0) and monthly follow-up questionnaires (T1-12) after randomization and 3 STI screening points for chlamydia (T0, T6, and T12). Cost and outcome data are being collected to compare the resource use and cost-effectiveness of the 2 HIS-UK delivery models compared to usual condom distribution care. The protocol for this trial was registered with the ISRCTN Clinical Trials Registry in October 2019.

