### Sample Size

The clinical effectiveness of HIS-UK delivered by ProHIS and e-HIS will be analyzed with an overall Type I error rate of 5% (2.5% per comparison), comparing test positivity in each of the intervention arms with the control arm (usual care). Data published by the National Chlamydia Screening Programme suggest a test positivity of 11.9% in 2017 and 12.2% in 2018 among young men aged 15-24 years in England tested in specialist and nonspecialist (including community-based) services [37]. Our trial is powered to detect a 45% reduction in chlamydia test positivity among our intervention arms—from 11% to 6% at 6 months after randomization. Previous piloting suggests that the intervention is likely to be equally effective across all stratification subgroups (deprivation, ethnicity, sexual orientation, and age) [22,23].

To have 85% power to obtain the projected difference in the outcome at T6, the study requires 476 participants in each of the arms (G*Power 3.1.9.2). To minimize risk to the trial and to reflect 36% attrition at follow-up (observed during feasibility testing) [22], a total of 2231 participants will be randomized.

It is estimated that it will take 30 months to recruit the target sample of 2231 young men, based on a recruitment rate of 15 per month, per NHS Trust site, using a phased recruitment strategy.

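### 476 per arm does not give 85% power at the stated 2.5% per comparison: power is about 70% two-sided, or about 79% if the 2.5% is one-sided

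*Protocol article*

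**What the plan says.** All the inputs are in the Sample Size section of the protocol article, apart from the allocation ratio, which is under Trial Design.

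- Error rate and comparisons: "overall Type I error rate of 5% (2.5% per comparison), comparing test positivity in each of the intervention arms with the control arm".
- Effect: a reduction in test positivity "from 11% to 6% at 6 months after randomization".
- Power and sample: "To have 85% power to obtain the projected difference in the outcome at T6, the study requires 476 participants in each of the arms". The software is given as "G*Power 3.1.9.2", without the test option or the number of tails.
- Attrition: 36%, giving 2231 to be randomised.
- Design: "randomized, controlled, superiority trial with 3 parallel arms (2 intervention and 1 control arm, with a 1:1:1 allocation".

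The Analysis section plans a generalized linear model on available cases for positivity at 6 months. It does not say whether tests are one- or two-sided.

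**The concern.** The section fixes alpha, effect, power and sample size together, so any one of them can be checked against the rest. A control rate of 11% against 6% at a Bonferroni-adjusted 2.5% ordinarily needs well over 500 per arm for 85% power, so 476 looked too small.

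This is the primary endpoint and the basis of the recruitment target. If the power is overstated, a null result for ProHIS or e-HIS would be read as coming from a comparison with a 15% chance of missing the planned effect. On the two-sided reading, that chance is about 30%.

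**Working it through.** **Inputs.** p1 = 0.11, p2 = 0.06, power 85%, 2.5% per comparison, 476 per arm, 36% attrition (Sample Size); 1:1:1 allocation (Trial Design). Sidedness is not stated, so both readings are shown.

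**Attempt to reproduce 476.** The pooled two-proportion formula is

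n = [z_α √(2p̄(1−p̄)) + z_β √(p1(1−p1) + p2(1−p2))]² / (p1−p2)²

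Here p̄ = 0.085, √(2 × 0.085 × 0.915) = 0.3944, √(0.0979 + 0.0564) = 0.3928, z_β = 1.0364 and (p1−p2)² = 0.0025.

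- Two-sided 2.5% (z = 2.2414): (0.8840 + 0.4071)² / 0.0025 = 666.8, so **667**.
- One-sided 2.5% (z = 1.9600; the same as two-sided 5%): (0.7730 + 0.4071)² / 0.0025 = 557.1, so **558**.
- One-sided 5% (z = 1.6449): (0.6487 + 0.4071)² / 0.0025 = 445.9, so **446**.

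Other methods do not close the gap:

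| Method | Two-sided 2.5% | One-sided 2.5% |
|---|---|---|
| Pooled z | 667 | 558 |
| Unpooled z | 664 | 555 |
| Arcsine | 655 | 547 |
| Log odds ratio (Wald) | 688 | 575 |
| Pooled with continuity correction | 707 | 597 |
| Fisher exact | about 697 | about 587 |

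None gives 476 at 2.5% per comparison; the smallest is 547.

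**What does give 476.** Full enumeration of the one-tailed Fisher exact test at alpha 5% gives power 0.8496 at n = 475 and 0.8503 at n = 476. So 476 is the smallest sample reaching 85% under that setting.

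**Power at 476 per arm.** The formula is

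power = Φ{[(p1−p2)√n − z_α √(2p̄(1−p̄))] / √(p1(1−p1) + p2(1−p2))}

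with 0.05 × √476 = 1.0909.

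- Two-sided 2.5%: Φ[(1.0909 − 0.8840)/0.3928] = Φ(0.527) = **70.1%**. Exact enumeration gives 70.5% for the z test and 66.8% for Fisher.
- One-sided 2.5%: Φ[(1.0909 − 0.7730)/0.3928] = Φ(0.809) = **79.1%**. Exact enumeration gives 79.7% for the z test and 76.3% for Fisher.
- One-sided 5%: Φ[(1.0909 − 0.6487)/0.3928] = Φ(1.126) = 87.0%. Fisher gives 85.0%.

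**Effect detectable with 85% power at 476, two-sided 2.5%.** Take p2 = 0.052, so p̄ = 0.081. Then Φ[(0.058 × 21.817 − 2.2414 × 0.3858)/0.3837] = Φ(1.04), about 85%. That is 11% to 5.2%, a relative reduction of 1 − 5.2/11 = 53%, against the 45% stated.

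**Attrition step.** 3 × 476 / 0.64 = 2231.25, which matches 2231. This step is right, and it returns 2231 × 0.64 / 3 = 476 evaluable per arm, with nothing spare. Carrying the other sample sizes through gives 3 × 667 / 0.64 = 3126.6 (about 3127 randomised, two-sided) and 3 × 558 / 0.64 = 2615.6 (about 2616, one-sided).

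**The case against.** Four points can be made for the plan.

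1. **The one-tailed 5% origin is an inference.** The article names the software but neither the test nor the tails. That is correct. The match is to the single participant, which is strong evidence but not proof. The inconsistency does not depend on it.
2. **The 70% assumes two-sided testing.** The article never says so, and the Discussion states a directional hypothesis. This stands as a qualification: on a one-sided reading the shortfall is smaller. But 76% to 80% is still below 85%, so neither reading rescues the statement.
3. **The 85% might be the chance that at least one arm succeeds.** If both arms reach 6%, simulation at two-sided 2.5% puts that chance at about 84.5%, close to the stated figure. The text does not claim this, though; the section frames the analysis as "comparing test positivity in each of the intervention arms with the control arm (usual care", arm by arm, and 476 falls just short even on this reading. Two other designs also come near 476: a three-arm 2-df chi-square test at 5% (464 per arm), and both interventions pooled against control at two-sided 2.5% (483 in the control arm). Neither is the design described.
4. **The fixed 2.5%/2.5% split is valid.** It controls the overall 5% and gives simple confidence intervals, which the Analysis section emphasises. This is right. The split is not the error; the error is that the sample size does not match it.

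**Conclusion.** The point holds. On the document's own inputs, 476 per arm does not give 85% power at 2.5% per comparison. Power is about 70% (67% Fisher) if tests are two-sided, the usual reading for a superiority trial with 5% overall, and about 79% (76% Fisher) if the 2.5% is one-sided. The shortfall is therefore roughly 5 to 18 percentage points across readings and tests. The attrition arithmetic is correct, but it carries the 476 straight into the 2231. These figures assume the planned rates of 11% and 6%, and exactly 476 evaluable per arm. The likely source, a one-tailed 5% Fisher calculation, is inferred.

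**What to change.** Keep the sample and correct the statement. State which test was used and that tests are two-sided, then write something like: *With 476 evaluable participants per arm, each comparison at two-sided 2.5% has about 70% power for 11% versus 6%; 85% power applies to 11% versus 5.2%.* If one-sided testing is really intended, say so and give about 79% instead. The cost is a change of wording and a less favourable stated power.

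If the sponsor wishes to keep 85% for 11% versus 6%, the target has to rise to about 3127 randomised (two-sided) or 2616 (one-sided) at 36% attrition.

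An optional improvement, on which this point does not depend, is to replace the fixed split with Holm or step-down Dunnett at overall 5%. If both arms reach 6%, simulation shows power per comparison rising from about 70% to about 76%, and power to show both arms from about 56% to about 67%, with no extra participants. Those gains require both arms to work, and the plan would need a sentence on how confidence intervals are then reported.

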### Process Evaluation and Trial Progression

The first 135 young men recruited and followed up for 6 months will form our internal pilot to assess trial implementation, participant responsiveness, intervention fidelity, and the acceptability of randomization and chlamydia screening for trial continuation. During the assessment, the following questions will be answered: “Can young men be recruited at a reasonable rate and to the numbers anticipated?” “Are young men willing to be randomized within the trial?” “Is chlamydia screening at T0 and T6 sufficiently acceptable and feasible to implement?” “Do young men remain in the study in sufficient numbers at 6-month follow-up?” “Are the intervention and study design sufficiently acceptable?” “Are site staff able to deliver the intervention with reasonable fidelity?”

To assess intervention implementation and engagement, participant access to and usage of e-HIS is recorded along with fidelity of ProHIS intervention delivery and completion of condom ratings. In-depth qualitative interviews with all site staff involved in the recruitment of internal pilot participants will also be conducted to explore acceptability of the research design and ease of trial delivery. Furthermore, at 6 months after randomization, internal pilot participants allocated to the ProHIS and e-HIS trial arms will be invited to participate in interviews to explore study acceptability, issues of contamination and protocol adherence, and intervention benefits. We expect that 20 interviews will be sufficient to reach theoretical saturation; however, if necessary, additional interviews will be undertaken with participants from subsequent recruitment phases.

### Analysis

Analysis and presentation of data will be in accordance with the revised CONSORT 2010 statement [38]. The statistical analysis will be performed on available cases following intention-to-treat principles with due emphasis placed on confidence intervals for the between-arm comparisons. Baseline demographics (eg, age, ethnicity, deprivation, and sexual orientation) and self-reported outcome measure data (secondary process indicators) will be assessed for comparability between the arms using descriptive analyses.

The primary analysis will be undertaken using generalized linear modelling to compare the effectiveness of HIS-UK against usual care in reducing chlamydia test positivity at T6. The analysis will be repeated at T12 to examine longevity of intervention effect. Analyses will be extended to include the investigation of possible intervention moderators and mediators, the exploration of process measures (eg, number of condom ratings completed), and the identification of which young men most benefit from ProHIS and e-HIS (according to age, sexual orientation, ethnicity, and social deprivation). Similar comparative analyses using the secondary process indicators collected at T0-T12 will be undertaken using generalized linear mixed modelling to allow for the analysis of repeated measurements over time and comparison between the study arms. To meet our intention-to-treat principles analysis, withdrawals and protocol violators will be analyzed in their arms as randomized.

To assess the costs and benefits of HIS-UK (delivered via ProHIS and e-HIS) compared with usual care, both a within-trial analysis and a model-based economic analysis will be undertaken. The main within-trial economic analysis will assess cost-effectiveness based on incremental cost per quality adjusted life year gained at 6 months, with a secondary analysis of cost per case of chlamydia avoided at 6 months, reflecting the primary outcome of the trial; this analysis will then be repeated to measure cost-effectiveness over a 12-month period. Initially, the base case analysis will be framed in terms of a cost-consequence analysis for the 3 trial arms, and data will be reported in a disaggregated manner on the incremental cost and important consequences assessed in the trial.

If the trial shows that ProHIS or e-HIS are effective in reducing chlamydia positivity and other condom use health behavior outcomes, compared with usual condom distribution care, there are likely to be important cost implications for the health care sector, the wider public sector, and for society as a whole. If deemed necessary, a decision-analytic model will be used to extrapolate costs and outcomes beyond the end of the trial and synthesize data on costs and outcomes from a range of sources [39]. The evidence used in the model will be drawn from the trial and a comprehensive review of the literature on condom use and failure, prevalence of chlamydia and other STIs, transmission rates, and long-term outcomes. If data availability permits, a public sector and an NHS perspective will be adopted, in line with recommendations [40].

The results will be presented using cost-effectiveness acceptability curves to show the uncertainty surrounding the cost-effectiveness of the ProHIS and e-HIS interventions, for a range of thresholds for cost-effectiveness [41]. Both deterministic and probabilistic sensitivity analyses will be used to explore the inherent uncertainty around the estimates employed in the evaluation [39].

### Ethics Approval

Ethics approval for the randomized controlled trial has been obtained from the University of Southampton Research Integrity and Governance Committee, and the Health Research Authority South Central Oxford B Committee (REC reference: 19/SC/0486).

## Results

Funding was secured in February 2019, and recruitment was commenced in March 2020; however, due to the COVID-19 pandemic, recruitment was halted in April 2020. As a result, the study was adapted to reduce clinical contact between recruitment site staff and participants (see “Post–COVID-19 Amendments”), and subsequently reopened to recruitment in July 2021, with a planned participant recruitment period of 30 months and a 12-month participant follow-up.

## Discussion

### Overview

The hypothesized main findings of this trial are that the HIS-UK intervention (delivered by either ProHIS or e-HIS) will reduce chlamydia test positivity among young men (16-25 years) by enhancing condom use experiences and improving correct and consistent condom use, as compared to usual condom distribution care. In addition, it is anticipated that the HIS-UK intervention, as compared to usual condom distribution care, will be cost-effective.

### Strengths and Limitations

The strengths of this protocol include the use of a randomized controlled trial design, the targeted large sample, and the use of chlamydia biomarker testing. A limitation of the design is the restriction of participants to men aged 16-25 years. Future directions include adapting and evaluating the intervention among women and men of a broader age range.

### Dissemination Plan

The results from this study will be presented at scientific conferences, published in peer-reviewed journals, and shared on social media. We will also share our findings with key stakeholders, including young men, clinicians, and commissioners of sexual health services.

### Conclusions

This is the first randomized controlled trial evaluation of the HIS-UK intervention with young men. If the intervention is effective and cost-effective, this could have a positive impact on NHS services by reducing the incidence of STI rates and relieving pressure on staff time, financial costs, and other resources in the treatment of STIs. The intervention may also encourage sexual health services to adopt additional digital technologies and ultimately improve access to such services for young people, decreasing health inequalities engendered by fear of stigmatization.

## Abbreviations

CUE: condom use experience
e-HIS: HIS-UK delivered digitally
HIS-UK: home-based intervention strategy
NHS: National Health Service
ProHIS: HIS-UK delivered face-to-face
SF-12: 12-Item Short Form Health Survey
STI: sexually transmitted infection
